## Abstract

**Background:**

Subarachnoid hemorrhage (SAH) accounts for 4.4% of cerebral vascular disease, which is one of the leading causes of death in China. Rupture of intracranial aneurysms (IAs) is the most common cause of SAH. The natural history of unruptured IAs (UIAs) and the risk factors for rupture are among the key issues regarding the pathogenesis of IA and SAH that remain unclear in the Chinese population.

**Methods:**

The China Intracranial Aneurysm Project (CIAP) is a prospective, observational, multicenter registry study of the natural courses, risk factors for the onset and rupture, treatment methods, comorbidity management and other aspects of intracranial aneurysms. To date, there are five studies in the CIAP. CIAP-1 is a prospective observational cohort study of UIAs. More than 5000 patients who will be followed for at least 1 year are expected to be enrolled in this cohort. These participants come from more than 20 centers that represent different regions in China. Enrollment began on May 1, 2017, and will take approximately 5 years. A nationwide online database of UIAs will be built. Participants’ basic, lifestyle, clinical and follow-up information will be collected. The blood samples will be stored in the Central Biological Specimen Bank. Strict standards have been established and will be followed in this study to ensure efficient implementation.

**Discussion:**

The natural course of UIAs in the Chinese population will be explored in this registry study. In addition, the risk factors for the rupture of the UIAs and the joint effect of those factors will be analyzed. The present study aims to create a nationwide database of UIAs and investigate the natural course of UIAs in China.

*Trial registration* The Natural Course of Unruptured Intracranial Aneurysms in a Chinese Cohort (ClinicalTrials.gov Identifier: NCT03117803). Registered: July 5, 2017

## Background

Cerebrovascular disease is one of the leading causes of death in China and contributes to a heavy disease burden [1]. The age-standardized prevalence, incidence, and mortality rates of stroke were 1114.8/100,000, 246.8/100,000 and 114.8/100,000 person-years, respectively, in China among those aged ≥ 20 years. Subarachnoid hemorrhage (SAH) accounts for 4.4% of cerebrovascular disease [2, 3]. Rupture of an intracranial aneurysm (IA) is the most common cause of SAH [4], which has very high morbidity and mortality [5]. A cross-sectional study of the community shows that the incidence of unruptured intracranial aneurysms (UIAs) is as high as 7% in the Chinese population of 35 to 75-year-old people [6]. Therefore, it is an urgent task to reduce the rupture risk and mortality rate.

It is critically important to clarify the natural history of UIAs and screen for risk factors for rupture. The International Study of Unruptured Intracranial Aneurysms (ISUIA) [7, 8] and Unruptured Cerebral Aneurysms Study (UCAS) [9] are the most influential studies of the natural course and annual rupture rate of UIAs. However, a relatively high degree of selectivity bias leads to lower external validity of their findings. There are still no reliable reports about the annual rupture rate of UIAs in Chinese populations.

Thus far, there is also a lack of a clear conclusion about the risk factors for rupture. Studies have shown that some factors might be related to the risk of aneurysm rupture, such as factors related to morphology (the largest diameter ≥ 7 mm, presence of ascus, etc.) [7] and pathological damage (endothelial instability, inflammatory cell infiltration, etc.). Racial factors also have a great deal of influence on the risk of aneurysm rupture. Scholars have established a “PHASES” UIA rupture prediction model based on the North American, Finnish, and Japanese populations through systematic reviews [10]. However, the results obtained by different research institutions are not consistent and might be impacted by research design and sample size. Thus, the applicability of the existing rupture model requires further verification [11].

Although a number of UIA studies have been successively carried out, the natural history of UIAs in the Chinese population is still unclear. The previous studies were mostly single-center, small-scale retrospective data analyses and cannot provide high-level research evidence. The main purposes of the present study are to calculate the annual rupture rate of UIAs in the Chinese population and identify possible risk factors for rupture.

### Study design and methods

The China Intracranial Aneurysm Project (CIAP) is a prospective, observational registry study of the natural courses, risk factors for the onset and rupture, treatment methods, comorbidity management and other aspects of IAs. To the best of the authors’ knowledge, the CIAP, sponsored by Chinese Science and Technology Ministry and National Stroke Prevention Project Committee, is the largest ongoing project evaluating IAs in China; it currently includes 5 studies. The first study in the CIAP was designed to set up and manage a UIA database of 5000 individuals and calculate the annual rate of rupture of those aneurysms. The second study aimed to identify the risk factors for aneurysm rupture and develop a multidimensional predictive model for rupture. The third study was designed to explore the strategy of antithrombotic therapy in UIA patients complicated by ischemic cardiovascular/cerebrovascular diseases. The fourth study was designed to compare the therapeutic effects of intervention surgery and craniotomy surgery in the treatment of UIAs. The fifth study was designed to develop a standardized clinical pathway for early-stage cerebral hemorrhage caused by aneurysms [12, 13].

CIAP-1, intended to establish an open research platform and a nationwide UIA cohort, is the first and most fundamental task of the entire project. It is designed to achieve the following aims:Establish a nationwide public health and research platform administered by researchers, doctors, clinical center managers, Contract Research Organizations (CROs) and health management companies.Establish a nationwide prospective UIA cohort as a joint effort from 20 clinical centers.Clarify the natural history and annual rupture rate of UIAs in China.Identify the characteristics of people with intracranial aneurysms and look for possible causes of IAs.Screen for risk factors for UIA rupture and provide guidance to CIAP-2, which is designed to establish a multidimensional model to predict UIA rupture.

### Participating center qualification

The investigators will collaborate with the other 19 medical centers located in the different regions of China (Southeast, Southwest, Northwest and Northeast China). Each center has more than two referral units, has experience in the diagnosis of UIAs and has a skilled treatment team. Thus, it is believed that this cohort can adequately represent the population at the regional and national levels. During the study period, all the patients included in this study will be observed and treated in the collaborating medical centers.

### Recruitment of participants

Patients will be enrolled consecutively in all of the clinical centers and through China’s Stroke Prevention Project Committee. Patients with UIAs will be enrolled when they first visit the clinical center or are registered by the Stroke Prevention Project Committee. Patients with multiple aneurysms will also be enrolled when at least one aneurysm remains untreated. The patients will be selected according to the following selection criteria.

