#### Inclusion criteria

Diagnosis of untreated unruptured intracranial aneurysms (by CTA, MRA or DSA).Modified Rankin Scale (mRS) score of 3 or less.Age older than 18 years.Provision of consenting to participate in the study.

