#### Exclusion criteria

Subarachnoid hemorrhage of unknown etiology.Other cerebral arteriovenous malformations or cerebral arteriovenous fistulas.Malignant tumor.Fusiform aneurysms.Aneurysms caused by trauma, mycotic or other factors.A life expectancy of less than 1 year.Participation in other clinical studies of intracranial aneurysms.Refusal of follow-up.

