### The plan and methods of follow-up

Every patient will be followed for at least 1 year if the aneurysm is not ruptured or treated by surgery. The Estimated Primary Completion Date is December 30, 2021. Thus, the follow-up procedure is expected to last until December 30, 2022. The participants will be contacted by phone or Internet at 3 months and 12 months and contacted face to face at 6 months. Images of computed tomography angiography (CTA)/magnetic resonance angiography (MRA)/digital subtraction angiography (DSA) and vascular ultrasound will be obtained at 6 months. The participants’ visit and evaluation schedule is shown in Table 1.

**Table 1 Tab1:** Participants’ visit and evaluation schedule

Visit number	Screening period	Follow-up period		
	1	2	3	4
Research arrangement	Screening	90 ± 14 days	180 ± 30 days	365 ± 30 days
Informed consent	√			
Selection criteria	√			
Baseline information	√			
History of disease and history of medicine taking	√			
Medicine taking		√	√	√
Symptoms and physical examination	√	√	√	√
Electrocardiogram	√			
Routine blood test	√			
Blood sugar	√			
Blood lipid	√			
Homocysteine	√			
Head CT/MRI	√	√	√	√
CTA/MRA/DSA	√		√	
Vascular ultrasound	√		√	
mRS score	√	√	√	√
HAMA score	√	√	√	√
End point evaluation		√	√	√
Adverse event evaluation		√	√	√

Participants should visit at least once a year after 1 year

*CT* computed tomography, *MRI* magnetic resonance imaging, *CTA* CT angiography, *MRA* magnetic resonance angiography, *DSA* digital subtraction angiography, *mRS score* modified Rankin scale score, *HAMA score* Hamilton anxiety score

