### Statistical methods

#### Sample size calculation

The sample size is calculated based on the following formula:$$ n = \frac{{u_{\alpha }^{2} p\left( {1 - p} \right)}}{{d^{2} }} $$

The annual rupture rate is expected to be 1% [9], the allowable error is d = 0.6%, the tests will be two-sided, with an α level of 0.05. It is calculated that 1173 subjects need to be enrolled in 1 year, and 4696 subjects are needed in 4 years. The expected drop-out rate is 5%. Drop-out is identified as enrolled patients who cannot be included in the primary analysis because, for example, they did not complete the follow-up in time or they lack key information.

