### Statistical analysis

Statistical description of the clinical data.Continuous variables are expressed as the mean ± standard deviation and compared by one-way analysis of variance. Categorical variables are expressed as the quantity (rate) and compared with the Chi-square test. Continuous variables that do not conform to a normal distribution are expressed using the median and interquartile range and are compared by the Mann–Whitney nonparametric test. P < 0.05 is considered significant.Annual rupture rate calculation.The overall annual rupture rate of UIAs is the proportion of aneurysms that ruptured in one year, which will be calculated with the data from the 1-year assessment. When analyzing the rate in a specific population, a subgroup analysis will be performed.Assessment of influential factors.Multivariate regression analysis will be used to calculate the OR of high-risk factors for the development and rupture of aneurysms. The 95% confidence interval will also be calculated. The receiver operating characteristic curve (ROC) will be used to determine the cutoff value with the best sensitivity and specificity for the prediction of rupture.

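### Newly detected and long-known aneurysms are pooled into one annual rupture rate, which may understate the first-year risk after detection; the rate should also be reported by time since diagnosis.

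*Protocol article*

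**What the plan says.** **Entry.** The section Recruitment of participants states: "Patients with UIAs will be enrolled when they first visit the clinical center or are registered by the Stroke Prevention Project Committee". It adds: "Patients with multiple aneurysms will also be enrolled when at least one aneurysm remains untreated". A patient already treated for one aneurysm can therefore enter with another.

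**Eligibility.** The diagnostic criterion is "Diagnosis of untreated unruptured intracranial aneurysms (by CTA, MRA or DSA"), with no date attached. Eight exclusions are listed, and none concerns time since diagnosis or earlier observation.

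**Rate.** The section Statistical analysis defines it so: "The overall annual rupture rate of UIAs is the proportion of aneurysms that ruptured in one year". The figure is taken from the visit at 1 year. Follow-up runs forward from enrolment: "Every patient will be followed for at least 1 year if the aneurysm is not ruptured or treated by surgery".

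**Context.** Participating center qualification says that each centre has more than two referral units. The Discussion quotes 5-year cumulative rupture of 40–50% for aneurysms above 25 mm and 0–2.5% below 7 mm, and acknowledges serious over-treatment of unruptured aneurysms in China. Neither Measures to reduce bias nor the limitations in the Discussion mention time since diagnosis.

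**The concern.** The clock starts at the first visit to a participating centre or at registration, not at detection. An aneurysm found years earlier elsewhere and still under observation qualifies on the same terms as one found this week. The earlier case has passed two filters before entry: it did not rupture and it was not treated.

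The article itself makes both filters plausible. Referral units make a diagnosis before the first centre visit a natural route in. Rupture risk that differs so strongly by size means that high-risk aneurysms leave the untreated, unruptured pool first, even if each aneurysm's own hazard is constant. Widespread treatment removes others, possibly selectively.

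The stake is how the main result is read. The study aims to describe natural history and to guide management. A reader who applies the pooled figure to the year after detection may be using too low a number. The mix may also differ between centres and between the two entry routes, which could look like a regional difference in risk. Enlarging the cohort does not remove either effect.

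**Working it through.** **Plan figures used.** Expected rate p = 1% and planned total 4696 (Sample size calculation). The stated precision is "the allowable error is d = 0.6%, the tests will be two-sided, with an α level of 0.05". The formula n = 1.96² × 0.01 × 0.99 / 0.006² gives 1057 before drop-out and 1113 with the stated 5%, not 1173. A 10% allowance gives 1174, and 4 × 1174 = 4696. That discrepancy is a separate matter. Here 4696 serves only as the cohort size, taken as one aneurysm per patient.

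**Step 1: can the bias be computed?** No. It needs the share *f* of long-known aneurysms and their 1-year risk *r* relative to newly detected ones. The document gives neither.

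**Step 2: range over assumed values.** With an assumed 1% first-year risk after detection, the pooled rate is 1% × [(1 − f) + f·r].

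| r | f = 25% | f = 50% | f = 75% |
|---|---|---|---|
| 1 | 1.00% | 1.00% | 1.00% |
| 0.75 | 0.94% | 0.88% | 0.81% |
| 0.5 | 0.88% | 0.75% | 0.63% |
| 0.25 | 0.81% | 0.63% | 0.44% |

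With r = 1 there is no bias at any f. If long-known cases reach a centre because the aneurysm has grown or become symptomatic, r could exceed 1. For example, r = 1.25 and f = 50% give 1% × (0.5 + 0.5 × 1.25) = 1.125%. The direction is therefore not fixed either.

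**Step 3: depletion from the article's own contrast.** Take two groups with 5-year rupture of 40% and 2.5%, the least extreme pair in the quoted ranges, and a constant hazard within each group. One-year risks are 1 − 0.60^(1/5) = 9.71% and 1 − 0.975^(1/5) = 0.505%. Assume the high-risk share at detection is 2% or 5%.

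- At detection: 0.02 × 9.71% + 0.98 × 0.505% = 0.69%; 0.05 × 9.71% + 0.95 × 0.505% = 0.97%.
- High-risk share among those unruptured after 5 years: 0.02 × 0.60 / (0.02 × 0.60 + 0.98 × 0.975) = 1.24%; likewise 0.05 × 0.60 / (0.05 × 0.60 + 0.95 × 0.975) = 3.14%.
- One-year risk in those survivors: 0.62% and 0.79%, which is 10% and 18% lower than at detection.
- A 50:50 mix: 0.65% and 0.88%, about 5% and 9% below the rate at detection, or 0.035 and 0.086 percentage points.

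Selective treatment before entry is not in this calculation.

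**Step 4: compare with random error.** The 95% half-width at n = 4696 is 1.96 × √(0.01 × 0.99 / 4696) = 0.28 percentage points. The Step 3 shifts are well inside it. In Step 2, only r = 0.5 with f = 75%, and r = 0.25 with f = 50% or more, exceed it (shifts of about 0.38 to 0.56 points).

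**The case against.** The stated objective is the annual rupture rate of unruptured aneurysms in the Chinese population, not the rate in newly detected ones. A consecutive mix of recent and known cases is a legitimate sample of untreated aneurysms under care, and the pooled figure describes it. This stands, and it is why the pooled rate should stay.

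A reader might infer immortal-time bias. The document does not support that: follow-up and the 1-year assessment run forward from enrolment, and no time before entry is counted. Detection is not onset either, so a newly diagnosed aneurysm has itself survived for an unknown time.

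A reader might also infer that the rate is 10–21% too low. That range needs an assumed later hazard of 0.8% per year, an assumed 2–4-fold hazard in the first 3 months after detection, and an assumed half of the cohort long-known. New-case rates are then 1.0–1.4% against mixed rates of 0.9–1.1%. None of these three inputs is in the document, and entry at the first visit will often fall close to diagnosis.

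Nor can one conclude that the diagnosis date is not collected. The data list is a condensed summary with open-ended categories, and Table 1 includes baseline information and disease history.

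Finally, the article plans stratified and subgroup analyses and says that influential variables will be considered when the rate is calculated. The means to handle this therefore exist, but time since diagnosis is not named, so the general wording does not secure its use.

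**Conclusion.** The point holds as a worthwhile improvement, not as an error in a stated figure. The entry rule and the pooled 1-year proportion, as fixed, mix aneurysms at different times since detection, and those known longest are selected for not having ruptured or been treated. The pooled rate may therefore understate the first-year risk after detection.

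The size is unknown. The article's own size contrast with an assumed 2–5% high-risk share and a half-and-half mix gives about 5–9%, which is small beside the sampling error. Larger shifts need a large share of long-known cases together with a much lower risk in them. With equal and constant hazards and no selective treatment there is no bias.

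The Discussion's closing aim concerns patients with different risk factors and does not single out the newly diagnosed. It would be wrong to read the pooled rate as invalid for the study's stated target.

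**What to change.** 1. Keep the pooled annual rupture rate as the figure for the enrolled cohort.
2. Make sure the date of first diagnosis is captured for each aneurysm at enrolment. If the case report form already holds it, nothing needs adding.
3. Prespecify a window that defines newly diagnosed (3 months before enrolment, for example). Report the rate for newly diagnosed and previously known aneurysms beside the pooled rate, with the share of each by centre and entry route.
4. Include time since first diagnosis in the risk-factor model, so that it is also available to CIAP-2.

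**Cost.** At most one date field, one definition, one extra stratum and one covariate; no patient is lost. Precision within strata falls. If half of 4696 are newly diagnosed and the rate is 1%, the half-width is 1.96 × √(0.0099 / 2348) = 0.40 percentage points against 0.28 pooled. Each stratum would then have about 23 ruptures (0.01 × 2348), so the stratum rates should be read as estimates with intervals rather than as a test of difference.

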#### Inclusion criteria

Diagnosis of untreated unruptured intracranial aneurysms (by CTA, MRA or DSA).Modified Rankin Scale (mRS) score of 3 or less.Age older than 18 years.Provision of consenting to participate in the study.

#### Exclusion criteria

Subarachnoid hemorrhage of unknown etiology.Other cerebral arteriovenous malformations or cerebral arteriovenous fistulas.Malignant tumor.Fusiform aneurysms.Aneurysms caused by trauma, mycotic or other factors.A life expectancy of less than 1 year.Participation in other clinical studies of intracranial aneurysms.Refusal of follow-up.

### Outcomes

The primary outcome: the rupture of the aneurysm.The secondary outcome: obvious changes in the morphology of the aneurysm (maximum diameter increase ≥ 1 mm or new daughter sac forms); or a new serious clinical symptom develops (such as headache).

### The plan and methods of follow-up

Every patient will be followed for at least 1 year if the aneurysm is not ruptured or treated by surgery. The Estimated Primary Completion Date is December 30, 2021. Thus, the follow-up procedure is expected to last until December 30, 2022. The participants will be contacted by phone or Internet at 3 months and 12 months and contacted face to face at 6 months. Images of computed tomography angiography (CTA)/magnetic resonance angiography (MRA)/digital subtraction angiography (DSA) and vascular ultrasound will be obtained at 6 months. The participants’ visit and evaluation schedule is shown in Table 1.

**Table 1 Tab1:** Participants’ visit and evaluation schedule

Visit number	Screening period	Follow-up period		
	1	2	3	4
Research arrangement	Screening	90 ± 14 days	180 ± 30 days	365 ± 30 days
Informed consent	√			
Selection criteria	√			
Baseline information	√			
History of disease and history of medicine taking	√			
Medicine taking		√	√	√
Symptoms and physical examination	√	√	√	√
Electrocardiogram	√			
Routine blood test	√			
Blood sugar	√			
Blood lipid	√			
Homocysteine	√			
Head CT/MRI	√	√	√	√
CTA/MRA/DSA	√		√	
Vascular ultrasound	√		√	
mRS score	√	√	√	√
HAMA score	√	√	√	√
End point evaluation		√	√	√
Adverse event evaluation		√	√	√

Participants should visit at least once a year after 1 year

*CT* computed tomography, *MRI* magnetic resonance imaging, *CTA* CT angiography, *MRA* magnetic resonance angiography, *DSA* digital subtraction angiography, *mRS score* modified Rankin scale score, *HAMA score* Hamilton anxiety score

### Collection and management of data

The basic information (name, sex, age, address, etc.), lifestyle information (smoking, sleeping, exercise, job, stress, etc.), clinical data (symptoms; signs; medical history of hypertension, diabetes, cardiovascular disease, and coagulation dysfunction; family history), imaging data (the number, location, size, and morphology of aneurysms as shown on medical imaging) and follow-up information (changes in images, symptoms, and living styles; drugs taken during follow-up; etc.) will be collected during the study.

An electronic data capture (EDC) system (http://www.ciastudy.com.cn) was constructed for this project. Data are collected in each center, recorded on Case Report Forms (CRFs) and then uploaded to the EDC system.

The CRF is divided into 2 books: CRF-A is the enrollment book, while CRF-B is the follow-up book. When the CRF-A is finished, its integrity and accuracy will be verified in a timely manner by a clinical research coordinator (CRC). Then, the CRF-A will be transported to the Information Managing Center (IMC) in Beijing and uploaded by a professional database administrator (DBA) into the EDC System. A double check of the data will be implemented by the EDC system. CRF-B will be transported to the IMC 1 year later, when the follow-up has been completed. The double-check process will also be implemented for the CRF-B. The CRFs will be transported back to and stored at the enrollment center when the data upload is completed and will be stored for at least 5 years after the end of the project.

Every researcher has an account with the EDC system, which has different permissions according to the researcher’s role. The CRC can scan the data into the EDC system but cannot modify it without the permission of the manager of the IMC. Every change in the patient’s information in the database will be recorded by the system. The CIAP-1 database will be maintained for at least 5 years after the end of this study. The EDC system will continue running for other studies in the CIAP.

The DICOM data of computed tomography (CT), magnetic resonance imaging (MRI), and DSA collected by the participating centers will be transported and stored at the Medical Image Analysis Center (MIAC) in Xuanwu Hospital. These DICOM data will be reanalyzed to achieve a unified interpretation to ensure the homogeneity of the data (Table 2)

**Table 2 Tab2:** The 20 participating centers in CIAP-1

